5. At this point, on Day 0 and Day 1, the inmate will be given another opportunity to opt-out of consenting to participate in the study and to have the swab HIV tested. If the inmate opts out and is part of the Day 0 or Day 1 testing group, s/he will be invited back for testing on Day 1 or Day 7, respectively. If the inmate is part of the Day 7 testing group, s/he will not be approached again for testing.
6. If the inmate provides written consent, s/he will be administered the standardized MacArthur Competency Assessment Tool by a member of the study staff. The competency assessment tool will determine if the inmate understands the purpose of HIV testing and the potential benefits and risks or discomforts of choosing to test.
7. If the staff member deems the inmate competent according to the standardized tool, the inmate’s swab will be tested for HIV and the inmate will participate in an interview. The interview will include standardized instruments to assess opiate and alcohol withdrawal, psychological distress, and medical ability to consent to treatment. The schedule for administering the questionnaire is detailed in Table 1 below. The inmate’s swab will be tested immediately. Testing will be performed by the research study staff. Results will be recorded, and the swab will then be discarded in a hazardous waste container.
8. If the inmate is deemed not competent according to the standardized tool, further interviewing will be halted. The swab will be immediately discarded in a hazardous waste container and will not be tested. The inmate will be informed that even though s/he has consented to be HIV tested, the study staff does not believe that now is a good time for him or her to be HIV tested. If the inmate is part of the Day 0 or Day 1 testing group, the study staff will inform the inmate that he or she will be invited back for testing in the near future. Inmates in all three testing groups will also be informed that if this is not satisfactory, then they can always request an HIV test from the HIV testing counselors.
9. To explore feasibililty among correctional medical and custodial staff members, we will conduct one on one interviews with nurses, HIV counselors, mental health personnel, drug treatment staff, health services administrative staff members, and custodial staff to explore their attitudes about routine HIV testing. We will approach those staff members involved with intake procedures as well as medical staff.

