Table 1: Schedule of Interviews

| **Interview Instrument** | **Administered to Inmate** | **Administered to Staff** |
| --- | --- | --- |
| MacArthur Competence Assessment to evaluate medical ability to consent to testing | X |  |
| Demographics | X |  |
| History of previous HIV testing experiences | X |  |
| Court dates | X |  |
| Likelihood of remaining incarcerated | X |  |
| Willingness to HIV test now if it were made available | X |  |
| Attitudes about HIV testing in jails and prisons | X |  |
| Clinical Opiate Withdrawal Scale (COWS) | X |  |
| Clinical Institute Withdrawal Assessment of Alcohol (CIWA) | X |  |
| National Center for Health Statistics (NCHS) K6 Scale for Serious Psychological Distress | X |  |
| Staff attitudes about routine HIV testing in jails |  | X |

3.A.5.2 Delivery of HIV Test Results

1. Timing of delivery of test results will differ depending on the testing group. For the Day 1 and Day 7 testing groups, delivery of test results will be given the same evening that testing occurs. For the Day 0 testing group, however, delivery of test results will be given the following morning instead of the night of intake. Although this protocol is to determine the feasibility of future implementation of a rapid routine HIV testing program, for the purposes of this study it is not logistically possible for us to deliver preliminary positive test results the night of intake. This is because delivery of preliminary positive test results must be done by the DOC HIV counselors. Because intake procedures only start around 9pm and continue very late into the night, it is not logistically possible for us to hire the DOC HIV testing counselors to work during those hours, as they must work the first shift (7am-3pm). Therefore, after extensive consultation with jail HIV testing counselors, nursing and medical staff, and [name], the HIV Prevention Program Manager for the Department of Corrections, we have decided to have delivery of all test results for the Day 0 testing group delivered early the following morning starting at 6:30AM. The counselors have agreed to be on call to come back during the 2nd shift (3pm-11pm) to deliver positive results to inmates tested on Days 1 and 7. For each facility, we have made these arrangements with HIV counselors who live in close geographic proximity to each jail.

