**5PM -9PM**

**MONDAY-FRIDAY**

**PHYSICIAN’S ASSISTANT** OFFERS TO SWAB INMATE FOR HIV TESTING AS PART OF ROUTINE CARE

**RESEARCH STUDY STAFF** OFFERS TO SWAB INMATE FOR HIV TESTING AS PART OF ROUTINE CARE

**INTAKE NURSE** OFFERS TO SWAB INMATE FOR HIV TESTING AS PART OF ROUTINE CARE

DOES NOT CONSENT

CONSENTS

DOES NOT CONSENT

CONSENTS

CONSENTS

RESEARCH STUDY STAFF CONSENTS SUBJECT FOR STUDY AND HIV TEST

RESEARCH STUDY STAFF CONSENTS SUBJECT FOR STUDY AND HIV TEST

RESEARCH STUDY STAFF CONSENTS SUBJECT FOR STUDY AND HIV TEST

COMPETENT

INTERVIEWED, SWAB TESTED

NO INTERVIEW, NO SWAB TESTED

INTERVIEWED, SWAB TESTED

NO INTERVIEW, NO SWAB TESTED

INTERVIEWED, SWAB TESTED

INCOMPETENT

COMPETENT

INCOMPETENT

COMPETENT

INCOMPETENT

RESULTS GIVEN **SAME EVENING**

RESULTS GIVEN **SAME EVENING**

NOT INVITED BACK FOR TESTING

INVITED BACK FOR **DAY 7** TESTING

RESULTS GIVEN **NEXT** **MORNING**

RESEARCH STUDY STAFF PERFORMS COMPETENCY ASSESSMENT

RESEARCH STUDY STAFF PERFORMS COMPETENCY ASSESSMENT

RESEARCH STUDY STAFF PERFORMS COMPETENCY ASSESSMENT

DOES NOT CONSENT

NO INTERVIEW, NO SWAB TESTED

INVITED BACK FOR **DAY 1** TESTING

INMATE OPTS OUT

INMATE SWABBED

INMATE OPTS OUT

INMATE SWABBED

INMATE OPTS OUT

INMATE SWABBED

3.A.7 Analytic Plan

Ineligibility for routine HIV testing will be defined as those inmates who are medically incompetent using the MacArthur Competence Assessment Tool or who are otherwise found to be suicidal or in need of psychiatric holding by DOC staff. To address the first hypothesis, we will compare the proportion of individuals who are ineligible in each testing group using Mantel Haenszel testing. Because we anticipate that as many as 50% of jail detainees will be released within the first 72 hours, we will compare the proportion who accept testing in each group using Mantel Haenszel testing. Last, we will conduct multiple logistic regression of all intakes to assess the correlates of accepting mouth swabs as well as the correlates of accepting HIV testing. Secondary variables of interest will include demographic characteristics (it is possible, for example, that non-whites may be less likely to accept testing), drug use characteristics, presence of psychological distress, addiction severity scores, and history of past HIV testing. Data from this component of the study will be used to determine the effect size of a larger randomized controlled trial of routine HIV testing in jails.

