Inmates who arrive on each intake night (Monday through Friday) will be assigned to one of three testing groups based on the total number of inmates proceeding through intake that night and their arrival times to the jail. One third of inmates will be assigned to be approached for routine HIV testing and study participation the night of intake itself during routine health screening and mental health assessment (9pm – 1am). One third of inmates will be assigned to be approached for routine HIV testing and study participation the evening following intake when all arriving inmates undergo a routine physical exam. The final third of inmates will be assigned to be approached for routine HIV testing and study participation seven days after arriving at the facility. These procedures have been described above in the previous section.

1. **Inclusion/Exclusion Criteria:** What are the criteria for subject inclusion or exclusion? How will eligibility be determined, and by whom?

All newly incarcerated inmates will be eligible to be approached for testing and inclusion in this study. Individuals who are suicidal or incompetent to consent will be excluded from the study. We will keep track of how many people are incompetent to consent, but we will not keep data on those individuals or carry out the testing. The standardized MacArthur Competence Assessment, as well as the clinical judgment of the DOC clinicians who put individuals on suicide watch or psychiatric holds will be used to determine whether or not someone is eligible to participate.

1. **Subject Population:** Provide a detailed description of the proposed involvement of human subjects. Describe the characteristics of the subject population, including their anticipated number, age range and health status.

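### The acceptance regression on all intakes relies on interview covariates that, at the assigned contact, exist only for inmates who accepted and were tested

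*Protocol*

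**What the plan says.** The protocol's Analytic Plan (3.A.7) states: "we will conduct multiple logistic regression of all intakes to assess the correlates of accepting mouth swabs". The same sentence adds acceptance of the HIV test as a second outcome. On covariates it says "Secondary variables of interest will include demographic characteristics", and it continues with "drug use characteristics, presence of psychological distress, addiction severity scores, and history of past HIV testing".

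The Schedule of Interviews in 3.A.5.1 lists "History of previous HIV testing experiences" and the K6 scale among the instruments given to inmates. Step 7 of the same section says of the interview: "The interview will include standardized instruments to assess opiate and alcohol withdrawal, psychological distress, and medical ability to consent to treatment".

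Steps 3 to 8 of 3.A.5.1, repeated under Process of Consent in Section VII, fix the order: swab offer, written consent, MacArthur assessment, and only then the interview. For an inmate who passes, the "swab will be tested for HIV and the inmate will participate in an interview". For one who fails, interviewing stops and the swab is discarded. Section VI (Inclusion/Exclusion Criteria) adds that incompetent inmates are counted but "we will not keep data on those individuals".

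Section VIII describes a correctional database holding entry and release dates, medical and psychiatric classification and court cases. Its planned use is demographic information about subjects. Section VII requests no waiver of consent.

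**The concern.** A regression of acceptance needs covariates on people who accepted and on people who did not. Here the data collection gives the interview covariates to the first group and withholds them from the second. The protocol fixes both the model and the collection sequence, and the two do not fit together. A later analysis plan could not recover values that were never collected.

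The stake is the only planned analysis of who accepts and who does not. Run as written, it would either fail or shrink without notice to a selected subset reported as all intakes. Imputing the missing values would not help much: no non-acceptor is interviewed at the assigned contact, so the imputed values would rest on assumption.

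**Working it through.** **1. Which covariates are observed, and for whom, at the assigned contact**

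| Covariate in 3.A.7 | Source in the protocol | Available for non-acceptors? |
|---|---|---|
| Past HIV testing | Interview | No |
| Psychological distress | K6 in the interview; Hypothesis 2 also mentions nursing mental health assessments | K6: no. Nursing assessment: made on entrants, but not in the Section VIII list of data sources |
| Drug use | No dedicated instrument; the schedule has only withdrawal scales (COWS, CIWA), given in the interview | No |
| Addiction severity | No instrument in the schedule | Not scheduled for anyone |
| Demographics | Interview and correctional database | Possible, if database access covers non-participants |

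Reaching the interview requires swab accepted = 1, consent = 1 and competent = 1, and the same step triggers the test. So for everyone interviewed at the assigned contact, swab acceptance = 1 and test acceptance = 1.

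**2. The protocol's own figures**

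The uptake rates are those in bold in the sample size table of 3.A.4: men 60% at intake and 76% afterwards, women 75% and 88%. With p̄ = (p1 + 2·p2)/3 and 2:1 allocation, the pooled two-sided formula is

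n = [1.960·√(1.5·p̄(1−p̄)) + 0.842·√(p1(1−p1) + p2(1−p2)/2)]² / (p2−p1)²

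- Men: p̄ = 0.707; (1.093 + 0.484)²/0.16² = 97.2, so 98 per arm, as stated.
- Women: p̄ = 0.837; (0.887 + 0.413)²/0.13² = 99.99, so 100 per arm, as stated.

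The other eight rows reproduce as well. The table is not at fault; it only supplies the rates.

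**3. Expected counts, with 100 per arm and the post-intake rate applied to both Day 1 and Day 7**

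- Men tested: 60 + 76 + 76 = 212 of 300; not tested 88 (29%).
- Women tested: 75 + 88 + 88 = 251 of 300; not tested 49 (16%).
- Together: 463 tested; 600 − 463 = 137 not tested (23%), with no interview covariates at the assigned contact.
- By arm, not tested: Day 0, 40 + 25 = 65; Day 1, 24 + 12 = 36; Day 7, 24 + 12 = 36.

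**4. Fit on complete cases**

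For men the outcome is 1 in 212 of 212, with variance 0. A logistic fit with one simulated interview covariate gave a perfect-separation warning, did not converge, and returned standard errors of 3413 (intercept) and 1224 (slope). No odds ratio exists.

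**5. Adding inmates tested on re-approach**

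Day 0 and Day 1 inmates who opt out or are found incompetent are invited back on Day 1 and Day 7. They number 65 + 36 = 101. The protocol gives no uptake for the second offer. If 25% to 50% were then tested (an assumption), about 25 to 50 zeros would have interview data. Acceptance in the fitted set would be 463/488 = 95% to about 463/513 = 90%, against 463/600 = 77% overall. All these zeros come from people who later accepted, measured one day (Day 0) or six days (Day 1) after the event being explained. The Day 7 arm would contribute 76 + 88 = 164 interviewed inmates and no zeros, so a term for that arm would still be perfectly predicted.

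**The case against.** The best reply is that the problem is selection and not impossibility, and that little depends on it.

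- **Re-approach.** A reader might infer that no refuser ever has interview data and that no coefficient can be computed at all. The documents do not support that. The re-approach in 3.A.5.1 and Section VII yields some zeros with covariates, and past testing barely changes over a few days. This stands. It does not rescue the planned model, because those zeros are a self-selected subset and none come from Day 7.
- **Other sources.** A reader might infer that the whole regression must be abandoned. Demographics are the first covariate group named, and the correctional database also holds psychiatric classification. A model with assigned time point and demographics is feasible. Whether database access reaches non-participants is unclear but not excluded: Section VIII speaks of subjects, and the HIPAA item in Section VII is answered only by an attachment that is not shown.
- **The count.** A reader might take 137 as the number of refusers. It is the number not tested, and it includes inmates who accepted the swab, consented and then failed the MacArthur tool. In the swab model those are acceptors. Halving Day 7 uptake for release would give 219 not tested (600 − 381), but released inmates were never offered a test. The protocol's own release figure is up to 50% within 72 hours, and 3.A.4 does not say whether its uptake rates already allow for release.
- **Aim 3.** A reader might infer that acceptability cannot be assessed. The primary outcome and the Mantel-Haenszel comparison of acceptance by group do not use interview data and are unaffected.
- **Importance.** The regression is secondary in a pilot, and neither the primary result nor the sample size rests on it. That is fair, and it limits the weight of the point without removing it.

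**Conclusion.** The point holds in a bounded form. For past HIV testing and K6 distress, the acceptance regression on all intakes has covariates only where the assigned-contact outcome is accepted. Their coefficients are inestimable on assigned-contact data, and seriously selection-biased if re-approached inmates are added. Addiction severity has no scheduled instrument, and drug use has no dedicated one.

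About 137 of 600 inmates (23%; 88 men and 49 women) would lack interview covariates at their assigned contact. This assumes 100 per arm, the bold uptake rates of 3.A.4, and the same rate on Day 1 and Day 7. What is lost is the explanation of who does not accept; the acceptance proportions by arm remain estimable.

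**What to change.** Reword 3.A.7 before the first intake:

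1. Fit the swab and test acceptance models on all assigned inmates, separately by jail, using only variables obtainable for everyone: assigned time point, intake night, arrival time, and demographics and medical and psychiatric classification from the correctional database.
2. Confirm that database access covers non-participants, or request it, since Section VIII refers only to subjects.
3. Remove the interview variables from these models. Use them only to describe interviewed inmates or compare them between arms, and state that such results are conditional on being tested.
4. Delete the addiction severity scores, or add a named instrument to the Schedule of Interviews.

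Asking every inmate about past testing before the swab offer is tempting but not recommended. It would collect research data before consent, with no waiver requested, and would alter the opt-out offer that the study sets out to simulate.

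The cost is a text change, permission for de-identified correctional fields on non-participants, and the loss of correlates that could not be validly estimated.

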## Section V: Research Involving Drugs, Devices or Biologics

Please note: protocols using chemicals, hormones, other natural substances, or devices not regulated by the U.S. Food and Drug Administration (FDA) must still complete this section of the application form. Based upon the information provided in items 1-4, the HIC will determine whether an Investigational New Drug (IND) or Investigational Device Exemption (IDE) application must be submitted to the FDA.

1. **Identification of Drug, Device or Biologic:** What is the name of the drug, device or biologic being used? Please identify whether FDA approval has been granted, and for what indication(s).
2. **Background Information:** Please provide a description of previous human use, known risks, and data addressing dosages, intervals, routes of administration, and any other factors that might influence risks.
3. **Source:** Please identify the source of the drug, device or biologic to be used.
4. **Preparation and Use:** Please describe the method of preparation, storage, stability information, and for parenteral products, method of sterilization and method of testing sterility and pyrogenicity.
5. **Use of an Investigational Drug, Device or Biologic:** Protocols which utilize a drug, device or biologic not approved by the FDA must provide the following information.

- What is the Investigational New Drug (IND) or Investigational Device Exemption (IDE) number assigned by FDA?
- For IDE’s: Did the FDA approve this IDE as a Category A (experimental/investigational) or as a Category B (non-experimental/investigational)?
- Who holds the IND or IDE?
- Is the drug or device provided free of charge by the Sponsor? Yes ___ No ___

1. The FDA requirements to qualify for an exemption from filing an IND are as follows [21 CFR 312.2(b)]:

Exemptions – The clinical investigation of a drug product that is lawfully marketed in the United States is exempt from the requirements filing for an IND if ALL the following apply:

- - 1. The investigation is not intended to be reported to FDA as a well controlled study in support of a new indication for use nor intended to be used to support any other significant change in the labeling for the drug;
    2. If the drug that is undergoing investigation is lawfully marketed as a prescription drug product, the investigation is not intended to support a significant change in the advertising for the product;
    3. The investigation does not involve a route of administration or dosage level or use in populations or other factor that significantly increases the risks (or decreases the acceptability of the risks) associated with the use of the drug product;
    4. The investigation is conducted in compliance with the requirements for institutional (HIC) review and with the requirements for informed consent of the FDA regulations (21 CFR Part 50 and 21 CFR Part 56);
    5. The investigation is conducted in compliance with the requirements regarding promotion and charging for investigational drugs and
    6. The investigation is not emergency research (21 CFR Part 50.24).

1. Use of Placebo: Does any part of the study involve placebo? Yes ___ No ___
   1. If yes, please address each one of the following:
      1. The safety and efficacy of other available therapies (if any).
      2. The maximum total length of time a participant may receive placebo on study.
      3. The greatest potential harm that may come to a participant as a result of not receiving effective therapy (immediate or delayed onset).
      4. Protocols in place to safeguard participants receiving placebo.

## Section VI: Human Subjects

1. **Recruitment Procedures:** How will potential subjects be identified, contacted and recruited? Attach copies of any recruitment materials – such as flyers, telephone scripts, or introductory letters – that will be used.

Please note that a researcher may not use an individual’s Protected Health Information (PHI) for recruitment into research without first obtaining an authorization from the individual, or a Waiver of Authorization from the HIC. A treating provider does, however, have the option to:

- Discuss with his/her own patients the option of enrolling in a study.
- Obtain written authorization from the patient for referral into a research study.
- Provide background information about the study to the patient so that the patient can initiate contact with the researcher.
- Provide the individual’s PHI to a researcher without authorization when the researcher has obtained an approved Waiver of Authorization for recruitment purposes from the HIC.

If PHI will be accessed without subject authorization, please state whether any member of the research team has an existing clinical relationship with the potential subject. Researcher-clinicians are permitted to access the PHI of their own patients, or patients of co-investigators listed on the protocol, for recruitment purposes. Alternately, please submit a completed Yale University Request for HIPAA Waiver of Authorization for Research Form (available at <http://info.med.yale.edu/hic/hipaa/>. *For further information, see the Yale HIPAA website at* <http://info.med.yale.edu/hipaa/>.

New entrants to the facilities undergo routine medical and psychiatric assessment each evening during the second (3pm-11pm) and third (11pm–7am) shift and are treated according to evidence-based protocols for management of acute intoxication, withdrawal or serious mental illness. They also undergo a physical exam the evening after intake processing. Recruitment for this study will take place during intake procedures, during the physical exam that happens the day after intake, and 7 days after intake during the second shift.

Inmates who arrive on each intake night (Monday through Friday) will be assigned to one of three testing groups based on the total number of inmates proceeding through intake that night and their arrival times to the jail. One third of inmates will be assigned to be approached for routine HIV testing and study participation the night of intake itself during routine health screening and mental health assessment (9pm – 1am). One third of inmates will be assigned to be approached for routine HIV testing and study participation the evening following intake when all arriving inmates undergo a routine physical exam. The final third of inmates will be assigned to be approached for routine HIV testing and study participation seven days after arriving at the facility. These procedures have been described above in the previous section.

1. **Inclusion/Exclusion Criteria:** What are the criteria for subject inclusion or exclusion? How will eligibility be determined, and by whom?

All newly incarcerated inmates will be eligible to be approached for testing and inclusion in this study. Individuals who are suicidal or incompetent to consent will be excluded from the study. We will keep track of how many people are incompetent to consent, but we will not keep data on those individuals or carry out the testing. The standardized MacArthur Competence Assessment, as well as the clinical judgment of the DOC clinicians who put individuals on suicide watch or psychiatric holds will be used to determine whether or not someone is eligible to participate.

1. **Subject Population:** Provide a detailed description of the proposed involvement of human subjects. Describe the characteristics of the subject population, including their anticipated number, age range and health status.

